## Statistical analysis

Baseline descriptive demographic data will be presented for the entire cohort. The primary outcome of median number of urinary frequency and incontinence episodes on a 3-day voiding diary at 3, 12 and 24 months will be compared to baseline for each patient using paired analysis. Secondary outcome measures including total AUA-SS, M-ISI, NBSS, SF-12, SSS and BCS scores at 3, 12 and 24 months will be compared to baseline for each patient using paired analysis. Continuous variables will be evaluated using paired t-test and categorical data will be analyzed using McNemar’s test. Paired data will be evaluated using a 2-sided paired t-test. Median values will be analyzed using a Wilcoxon signed rank test. Statistical significance will be considered with *p* < 0.05.

In order to assess for predictors of improvement of symptoms response to PTNS, planned subgroup analysis will be performed stratifying patients based on gender, EDSS score, and burden of disease on MRI. Furthermore, an interim analysis at evaluating outcomes at 3 and 12 months after PTNS is planned.

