**Exclusion Criteria**	
Age less than 18 years	
Indwelling catheters (urethral or suprapubic)	
currently pregnant or planning pregnancy	
Unable to attend weekly office visits for PTNS	
urodynamic findings of bladder outlet obstruction	
History of:	
bladder reconstruction (augmentation cystoplasty, catheterizable channel)	
cystectomy	
bladder stones	
pacemaker or defibrillator	
malignancy of bladder	
sacral neuromodulation	
intravesical injection of onabotulinum toxin within 9 months	

The PTNS procedure will be performed per the manufacturer’s specifications using a Neuromodulation System (Urgent® PC, Minnetonka, MN), as previously described [15]. Participants will undergo treatment for 30 min, once per week for 12 weeks. After 12 weeks, those with more than 50% improvement in symptoms based on a visual analog scale, will be offered maintenance PTNS sessions for 30 min every 28 days for a total of 24 months.

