### Follow-up and retention

Efforts will be made to follow-up all patients through 24 months after time 0 (initiation of PTNS). This is inclusive of patients who do not have an improvement of symptoms with initial 12 weeks of PTNS and do not pursue maintenance PTNS. In order to promote follow-up and retention, participants will be offered the opportunity to complete questionnaires in person or electronically, via a Research Electronic Data Capture (REDCap) [25]. Furthermore, participants will be compensated at the time of return of a 3-day voiding diary at times 0, 12, and 24 months.

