### Sample size

In this descriptive study, we aim to enroll at least 50 participants. While it is likely that the count of episodes in each of the time frames follows a Poisson distribution, the difference statistic could very well be expected to follow a normal distribution. If not, appropriate transformations would be applied to create an approximately normal distribution. Allowing for up to a 10% dropout rate, this sample size will provide a 95% chance to have a 95% confidence interval for our change statistic that is within +/− 1/3 of a standard deviation. In other words, if we have an underlying standard deviation of 3 for the difference in counts, simulation results indicate that over 95% of the time, the 95% confidence interval for the change statistic would fall within the mean +/− 1. This will provide sufficient precision for our outcomes of interest.

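### The visit-by-visit paired tests use only patients with both diaries, so the 12- and 24-month results risk leaning towards responders if non-responders return fewer diaries

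*Protocol article*

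**What the plan says.** The Statistical analysis section fixes the method. The primary diary outcome "at 3, 12 and 24 months will be compared to baseline for each patient using paired analysis", and the secondary scores are treated in the same way. Two tests are named that could apply to the diary counts: "Paired data will be evaluated using a 2-sided paired t-test" and "Median values will be analyzed using a Wilcoxon signed rank test".

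Under Study design and population, after Table 2, patients with more than 50% improvement on a visual analog scale after 12 weeks "will be offered maintenance PTNS sessions for 30 min every 28 days for a total of 24 months". No PTNS sessions are scheduled after that for the others.

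Follow-up and retention plans to follow every patient to 24 months. It expressly includes those who do not improve and do not go on to maintenance. Questionnaires may be completed electronically, and "participants will be compensated at the time of return of a 3-day voiding diary at times 0, 12, and 24 months".

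The Sample size section gives the only figures on loss: "we aim to enroll at least 50 participants", and "Allowing for up to a 10% dropout rate, this sample size will provide a 95% chance" of the stated precision. It gives no loss by visit or by response.

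**The concern.** A paired t-test or Wilcoxon signed rank test at month 24 takes nothing from a patient whose month-24 diary is missing, even when baseline and month 3 are on file. After week 12 the design separates patients by response: responders are seen every 28 days, and non-responders have no treatment visits. If diary return follows that split, the patients analysed at 12 and 24 months contain a larger share of responders than the cohort does, and the three visits describe different groups.

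This touches the main purpose of the study. The Background asks whether efficacy can be maintained in a progressive disease, and the Discussion asks whether monthly maintenance is adequate. An apparently stable effect from month 3 to month 24 could then be due in part to the loss of treatment failures. The value that predicts this loss, the month-3 response, is collected but not used by these tests.

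**Working it through.** **The plan's own figure.** The documents give no figure for attrition bias. The nearest is the precision statement: a 95% chance that the 95% CI lies within 1/3 SD. With half-width t(0.975, n-1) × s/√n, that chance is 95.8% at n = 50 but 86.0% at n = 45 (50 less 10%). This is a separate matter and is used here only for scale. At n = 45 the half-width is about 0.300 SD, or 0.300 × 3 = 0.90 counts at the plan's SD of 3.

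**Inputs for the bias.**
- Overall loss of 10%: Sample size section.
- Non-responder share of 28%: assumed. It follows 8/29 in Table 1 (29 initial, 21 on maintenance), but Table 1 does not say that the other 8 were non-responders. The Background gives improvement rates of 33% to 89%, so the wider range is shown as well.
- Change of -3 voids/day in responders and 0 in non-responders: assumed.
- For the simulation, assumed: n = 50, baseline 9/day, between-patient SD 2.5, within-visit SD 1.2, SD of individual change 1.0.

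**Formula.** Let p be the responder share, and qR and qN the loss in responders and non-responders. The responder share among completers is p(1-qR) / [p(1-qR) + (1-p)(1-qN)]. The completer mean is -3 times that share, and the true mean is -3p.

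**All of the planned loss on non-responders.** With qR = 0, qN = 0.10/0.28 = 0.357. The completer share is 0.72/0.90 = 0.80, and the completer mean is -3 × 0.80 = -2.40. The truth is -3 × 0.72 = -2.16. The ratio is 2.40/2.16 = 1.11. It equals 1/0.90 for any p as long as non-responders do not change. In absolute terms the shift is 0.24 voids/day, and 0.11 to 0.30 for p from 33% to 89%.

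**Likelihood comparison.** The 24-month change was regressed on baseline and month 3 in completers and then predicted for all patients. With baseline and month 3 complete, this is the maximum-likelihood estimate under an unstructured normal model for those three visits. Month 12 was not simulated.

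| Responders | Loss, non-responders vs responders | Overall loss | Truth | Completers | Likelihood |
|---|---|---|---|---|---|
| 72% | 10% vs 10% | 10% | -2.16 | -2.16 (0%) | no bias |
| 72% | 35.7% vs 0% | 10% | -2.16 | -2.41 (11 to 12%) | -2.24 (3 to 4%) |
| 89% | 50% vs 5% | 9.95% | -2.67 | -2.82 (6%) | -2.72 (2%) |
| 72% | 50% vs 5% | 17.6% | -2.16 | -2.49 (15%) | -2.26 (5%) |
| 72% | 80% vs 5% | 26% | -2.16 | -2.77 (28%) | -2.37 (10%) |
| 33% | 50% vs 5% | 35% | -0.99 | -1.45 (46%) | -1.10 (11%) |

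Overall loss is (1-p)qN + p·qR, for example 0.28 × 0.50 + 0.72 × 0.05 = 17.6%. A repeat of the second row gave -2.40 and -2.22, so these figures are good to about 0.02. In the 72% and 89% rows the standard errors of the two estimates are about equal.

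**The case against.** The strongest reply is that the plan has already addressed the mechanism. Non-responders are to be followed to 24 months, may answer electronically, and are paid for the diary at months 12 and 24, the two visits in question. The EDSS assessment is also annual for everyone. Lack of treatment visits is therefore not lack of study contact. This stands, and it is why the point is a risk and not an established bias.

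Three further replies have force. The last three table rows imply 18% to 35% loss, well above the planned 10%, so they show only what happens if retention fails. Within the planned loss the shift is small beside the precision sought: 0.24/3 = 0.08 SD against 1/3 SD. And the primary outcome is described as a median, whereas the calculation concerns means.

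A further reply is that missing-data handling may sit in an analysis plan that is not shown. That is fair, and the absence of such text is not the complaint. The complaint is about the tests that the article names, which by construction need both values.

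Two stronger readings are not supported. A reader might infer that the later results will overstate benefit. No passage says that non-responders will be lost more often, and equal loss gives no bias. A reader might also infer that the absence of payment for the month-3 diary is a second source of bias. Month 3 closes the weekly sessions, when patients are still attending, and nothing in the documents points to poor or selective return at that visit.

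**Conclusion.** The concern holds as a conditional risk. The named tests are complete-case at each visit, and the design makes loss related to response plausible. If the whole planned 10% loss fell on non-responders with no change, the 24-month mean change would be overstated by about 11% (-2.41 against -2.16 voids/day under the assumed values). A likelihood analysis using the earlier visits would cut this to 3 to 4% at about the same standard error. If loss is unrelated to response, there is no bias. The size rests on assumed response shares, effects and loss patterns, none of which the documents give. The shift is smaller than the planned precision, but it has a known direction and a larger sample would not remove it.

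**What to change.** Make the main analysis a maximum-likelihood repeated-measures model over months 0, 3, 12 and 24, including every patient with a baseline diary. It can be linear with unstructured covariance, or a negative-binomial mixed model for the counts. Report the change from baseline with its 95% CI at each visit. Keep the paired t-test and Wilcoxon signed rank test as completer analyses, and report diary return at each visit by maintenance status, so that readers can see whether loss did follow response.

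The cost is a change of analysis wording and slightly more programming. The main contrast becomes a mean or rate change, so the median and the Wilcoxon result should be reported alongside. The model reduces the bias but does not remove it, because a month-3 diary reflects response status only imperfectly.

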### Study outcomes

The primary outcome will be change in the median number of urinary frequency and urinary incontinence episodes on a 3-day voiding diary [37]. Secondary outcomes will be change in AUA symptom score (AUA-SS) and bothersome score, Michigan Incontinence Symptom Index (M-ISI), Neurogenic Bladder Symptom Score (NBSS), and from the Multiple Sclerosis Quality of Life Index (MSQLI) the Health Status Questionnaire (SF-12), Sexual Satisfaction Scale (SSS), and Bowel Control Scale (BCS) [28, 30–33].

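### The primary diary outcome is defined as a median, its precision is stated for a mean, two tests cover it, and the stated 95% assurance is not met at 45 completers for any candidate estimate

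*Protocol article*

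**What the plan says.** All references are to the protocol article.

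- **Study outcomes:** "The primary outcome will be change in the median number of urinary frequency and urinary incontinence episodes on a 3-day voiding diary". The Methods/Design part of the Abstract also uses the median.
- **Statistical analysis, primary outcome:** the median number of "episodes on a 3-day voiding diary at 3, 12 and 24 months" "will be compared to baseline for each patient using paired analysis". This sentence names no test.
- **Statistical analysis, tests:** "Paired data will be evaluated using a 2-sided paired t-test". The next sentence reads "Median values will be analyzed using a Wilcoxon signed rank test".
- **Sample size:** "we aim to enroll at least 50 participants". "Allowing for up to a 10% dropout rate", this number is said to give a 95% chance that the 95% confidence interval for the change statistic is within one third of a standard deviation. The worked example takes an SD of 3 for the difference in counts and an interval within 1 of the mean. The differences are expected to be normal. "If not, appropriate transformations would be applied to create an approximately normal distribution".

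**The concern.** Three parts of the plan describe the primary result differently. The outcome definition points to a median. The precision statement is about a mean. The test sentences overlap on the diary data, because these are paired and are also called medians.

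The candidate summaries are different quantities when counts are skewed. As an illustration with assumed data (negative binomial baseline counts with mean 9, halved at follow-up), the mean difference is -4.5, the median of the differences is -3 and the difference of the two medians is -4. The signed rank test addresses a change in medians only if the differences are symmetric. After a non-linear transformation, a margin of 1 is no longer in episodes.

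At stake is whether a reader can tell in advance which number is the primary result, and whether the precision that justifies the sample size applies to it.

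**Working it through.** **Inputs.** Enrolment of 50 and dropout of 10% (Sample size) give 50 × 0.90 = 45 completers. The target half-width is SD/3, which is 1 episode at SD 3. The confidence level is 95% and the stated chance is 95%. Differences are taken as normal, as that section expects.

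**Mean with paired t interval.** The half-width is t(0.975, n-1) × s/√n. Because (n-1)s²/SD² follows a chi-square distribution with n-1 degrees of freedom,

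P(half-width ≤ SD/3) = P(χ² with n-1 df ≤ n(n-1)(1/3)²/t²).

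- n = 50, the plan's figure: t = 2.0096, bound = (50 × 49/9)/4.038 = 67.4, probability 95.8%. This matches the stated 95%.
- n = 45, after the stated dropout: t = 2.0154, bound = (45 × 44/9)/4.062 = 54.2, probability 86.0%.

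Simulation with 200,000 runs agreed (95.9% and 86.0%). Poisson-based differences with SD 3 gave 95.4% and 85.5%. The smallest number of completers that gives 95% is 50, which needs 50/0.90 = 55.6, so 56 enrolled.

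**Hodges-Lehmann estimate**, with the interval from ordered pairwise averages that matches the Wilcoxon test: simulated.

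**Sample median**, with the order-statistic interval: simulated. Its actual coverage is 96.4% at n = 45 and 96.7% at n = 50, so it is slightly wider than a nominal 95% interval.

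| Estimate | 50 completers: half-width, chance of ≤ SD/3 | 45 completers: half-width, chance of ≤ SD/3 |
|---|---|---|
| Mean, paired t | 0.284 SD, 95.8% | 0.300 SD, 86.0% |
| Hodges-Lehmann, Wilcoxon | 0.291 SD, 90% | 0.309 SD, 75% (77% in a second simulation) |
| Sample median | 0.384 SD, 29% | 0.397 SD, 25% |

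Half-widths for the mean are t/√n. The others are simulated averages. The sample median would need about 110 completers to reach 95%.

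**Other readings of the criterion for the mean at n = 45.** Using z in place of t with an estimated SD gives 91.3%. Requiring the whole interval to lie inside the true mean ± SD/3 gives 19%. Two readings do clear 95%: treating the SD as known (half-width 0.292 SD, always met) and asking only that the point estimate be within SD/3 of the truth (97.5%). The first leaves no chance element to state, and the second is not a statement about an interval.

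**The case against.** The strongest reply is that the sentence on medians is a specific rule and the sentence on paired data a general one. Read that way, the Wilcoxon test governs the diary outcome and the t-test governs the questionnaire scores. This is a reasonable reading, and it narrows the conflict. The text does not state it, and it leaves the precision statement attached to a mean.

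A second reply is that the median may be each patient's median over the diary days. The mean change in those values could then use the t-test and the mean-based precision. The wording allows this but does not say it, and the assurance would still be about 86% at 45 completers.

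Several stronger readings are tempting, but the document does not support them:

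- A reader might infer that two or three p-values will be produced and one chosen afterwards. Overlapping sentences leave this possible but do not plan it. The transformation clause stands only in the Sample size section, and the Statistical analysis section assigns no transformation.
- A reader might infer that the primary result must be a difference of cohort medians, to which the mean-based precision cannot apply. The per-patient reading remains open.
- A reader might infer that the planned interval misses SD/3 on average. That is true of a raw sample median. The interval matching the Wilcoxon test averages about 0.31 SD, below 1/3. The shortfall lies in the probability of meeting the target.
- A reader might compute a different SD from the 9 versus 6 voids cited in the Discussion. That requires taking these as per-day means, which the text does not state. The SD of 3 is itself only a conditional example, and the target in SD units does not depend on scale.
- A reader might conclude that the median has to be abandoned. Either a mean or a median-type estimate is defensible if named in advance.

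The study is called descriptive, but it still sets a significance level of 0.05, and a descriptive study relies on a defined estimate with its interval.

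**Conclusion.** The inconsistency is real and lies within the document, so it is not detail left to an analysis plan. The outcome is a median, the precision is for a mean, and two test sentences cover the same data without an order of precedence.

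Read as a condition on the half-width of the interval, the stated 95% is not delivered after the stated 10% dropout for any of the three candidate estimates: about 86% for the mean, 75 to 77% for Hodges-Lehmann and 25% for a sample median. These figures assume normal differences and exactly 45 completers. Skewed counts would change them, and more than 50 enrolled would raise them. For the mean the gap is modest, since the typical half-width of 0.300 SD is still below 1/3. The point should be corrected, but it does not undermine the design.

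**What to change.** 1. Define one patient-level change variable on a stated scale, for example the change in episodes per 24 hours over the three diary days, separately for frequency and incontinence.
2. Name one estimate in advance with its matching test and interval: either mean change with the paired t-test, or the Hodges-Lehmann estimate with the Wilcoxon signed rank test. Make the other a sensitivity analysis.
3. Remove the data-dependent transformation clause from Sample size.
4. Use the same wording in the Abstract, Study outcomes, Sample size and Statistical analysis.
5. Restate the precision for the chosen estimate at 45 completers, for example about 86% rather than 95% for the mean, and give the scale of the SD 3 example. If the sponsor wants to keep 95% for the mean, the arithmetic above gives 56 enrolled.

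The cost is wording in four places and a less favourable precision statement. Data collection does not change. This settles the estimate and test for each comparison. It does not by itself single out one of the two counts or three time points as primary.

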## Discussion

The current literature regarding outcomes of PTNS in patients with MS who suffer from refractory lower urinary tract symptoms is favorable and is summarized in Table 1 [16–22, 38]. In 2009 Kabay published 3-month clinical outcomes in 19 patients showing significant decrease in mean overactive bladder questionnaire (OAB-V8) scores (15.7 vs 7.6, *p* < 0.05) [18]. Additionally they found a 40% complete response for urinary incontinence, and 58% complete response for urinary frequency on bladder diaries [18]. In 2011, Gobbi reported 3 month results in 18 patients from a multicenter, open label trial which found that there was statistically significant improvement in frequency (9 vs 6 voids, *p* = 0.04) and nocturia (3 vs 1 episodes, *p* = 0.002), additionally there was a 70% treatment satisfaction and significant improvement in the patient perception of bladder condition (PPBC) and patient perception of intensity of urgency scales (PPIUS) as well as the King’s Health Questionnaire (KHQ) [19]. The same group published long term outcomes (mean 24 months, range 15–41) which included variable maintenance PTNS every 2–4 weeks, in 83 patients [20]. They reported 89% had greater than 50% improvement on the PPBC at 12 months and 82% had treatment satisfaction and improvement in PPBC at 24 months [20]. Of the 74 patients undergoing maintenance, the mean monthly treatment frequency was 1.8 sessions [20]. Most recently, Canbaz Kabay published 12-month outcomes in 29 patients, with 21 patients undergoing maintenance PTNS at variable intervals between 2 and 4 weeks [22]. Similar to prior studies, they found significant improvements in frequency, nocturia, urgency, and incontinence at 3, 6, 9 and 12 months of follow-up [22]. Furthermore, they found that there was significant improvement on International Consultation on Incontinence Questionnaire-Short Form (ICIQ-SF), OAB-V8 and OAB-q at 12 months [22].

Prior literature suggests that PTNS will improve LUTS in patients with MS, and that results may be sustained up to 24 months with maintenance therapy. However, the literature is limited in several ways. First, only two prior studies report outcomes beyond 3 months, in a total of 95 patients [20, 22]. Next, the published maintenance schedules for PTNS in MS have varied between every 2–4 weeks, which makes it difficult to assess whether monthly maintenance PTNS is adequate for sustained efficacy [20, 22]. Furthermore, all prior studies have excluded patients with EDSS greater than 7 [16–22, 38]. Since patients with greater EDSS scores have increased disability, the impact of progressive MS patients who require assistive devices or wheelchairs for mobility is unknown. Finally, prior studies did not assess how early MS would respond to treatment. In light of ours and others’ studies showing RRMS are associated with more bothersome urinary symptoms, it will interesting to see how the treatment will affect early MS with EDSS less than 2 and if disease progression impacts PTNS efficacy [7, 23].

Another significant knowledge gap is that health related quality of life (HRQOL) has been reported in only one study and no prior studies have reported on potential improvements in bowel and sexual function with PTNS [19]. Evaluating the impact on HRQOL provides data to guide clinicians and patients on whether the investment in PTNS is worthwhile for overall health. Assessment of bowel and sexual function outcomes may expand the applications for PTNS in this population. Finally, none of the previous PTNS studies have incorporated MRI measures. As another novel exploratory measure, our protocol will also incorporate retrospective MRI data of the participants, obtained for routine neurologic surveillance, before and after PTNS in order to evaluate whether brain and spinal cord lesion location, T2 lesion number and volume changes, and disease burden impact track with PTNS treatments.

